## Background

At present, EEGs can only be recorded with considerable effort over a prolonged period of time under the everyday conditions of the patient. Patients are also unable to place an EEG cap on their own. To address these issues, a portable dry electrode EEG recorder (Fourier One) was developed. This new EEG device, which is integrated into a patient-friendly cap, records brain waves continuously or patient-controlled over a longer period of time. The patient can place the portable EEG device independently without the help of medical staff. With the development of this new EEG device, it is also possible to record brain waves outside medical facilities over a period of time ranging from several hours through to days under everyday conditions in the patient’s home. This results in new possibilities for the differential diagnosis of suspected cases of epilepsy, unclear consciousness disturbances, sleep disturbances, ADHD, or other disorders of the CNS, in contrast to other causes. The use of the new EEG device might also result in changes in the therapeutic management (e.g., changes in medication). These possible changes are summarized under the term “change-of-management” and reflect the therapeutic yield of a patient-controlled EEG home-monitoring. In this regard, the new portable dry electrode EEG recorder is intended to be used for both diagnostic performance and part of the therapeutic management.

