## Methods/design

### Study phases and settings

The portable EEG monitoring will be performed with patients of neurologist practices. A total of 18 participating specialists from the Saxony-Anhalt region have agreed to the study concept, including an advisory second opinion by the University Department of Neurology Magdeburg (KNEU). The practicing neurologists remain responsible for the medical care of their patients.

The HOME^ONE^ study consists of two phases:

During the *pilot study phase* (first phase), an EEG examination with the portable EEG system (F1) will be carried out with a population of approximately 130 study patients in addition to the conventional EEG approach *in the practices of* private practitioner*s*. As such, two EEG recordings will be performed during one consultation (but in sequence) with all other things being equal. This phase will examine the technical usability and efficacy of the new portable dry electrode EEG recorder and compare it with the different conventional practice EEG devices. It will also draw conclusions about the conformity of the reporting physicians. It is, hence, useful to “calibrate” the physicians, especially those from the KNEU who are responsible for performing the second assessment, before the beginning of the second phase. The inter-rater reliability of EEG evaluations shows kappa values of 0.5 to 0.9 [8–11], depending on the question. As an example, experienced epileptologists feel safe in their findings but have only low inter-rater matches [12]. It cannot be excluded that the additional use of the portable EEG device in neurological practice can already provide a diagnostic, therapeutically useful gain in knowledge.

During the *feasibility study phase* (second phase), the EEG examination will be carried out with approximately 500 study patients. This will commence with a conventional EEG in the doctor’s practice. Subsequently, the neurological practice will introduce the patient to the functioning and handling of the portable EEG device and the necessary accessories. Afterwards, the patient will be able to independently place and remove the portable EEG device and to use it in his or her home environment according to the dispositions of the neurologist.

The doctor in charge will determine the recording time with the cap according to medical criteria. The effective recording time will be included in the empirical evaluation.

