2B	Targeted referral for further clarification or co-treatment or further treatment^a^
2C	Initiate or change therapy (adjust, switch, settle)

^a^If clarification or therapeutic clarity can only be established by targeted referral, this clarification is part of the contractual medical care, not the study

In a first simplified evaluation level, the combinations (1A and 2A) as well as ((1B or 1C) will be (2B or 2C)) concordant. This results in Table 3.

**Table 3 Tab3:** Test assessment of conventional and portable EEGs by the private practitioner

Practice EEG	Portable EEG		Total
	Action (2B, 2C)	No action (2A)	
Action (1B, 1C)	a	b	a + b
No action(1A)	c	d	c + d
Total	a + c	b + d	a + b + c + d

This represents an intra-individual method comparison with a binary result criterion (“change of management”): The case management sequences of the portable EEGs are the same as those of the conventional practice EEGs (a or d), they are beyond (c) or remain behind (b). No decision should be made at this level (c) being “better” than (b).

To develop patients’ acceptability, we will use a questionnaire to measure relevant factors.

In an extended evaluation level, the results of the portable EEG will be more differentiated by means of the possibilities shown in Table 4.

**Table 4 Tab4:** Differentiation possibilities of the portable EEG results in an extended evaluation level

2A	No action or follow-up appointment only
2B1	Referral to the same specialist as 1B
2B2	Referral to a specialist different than 1B
2C1	Same therapeutic decision as 1C
2C2	Other therapeutic decision than 1C

The combinations of 1A with 2A are concordant with 1B with 2B1 and 1C with 2C1. The other combinations are discordant. Since the expected number of discordances is higher than the previous simplified classification, more cases than stated above will be required.

In the second part of the documentation, the attending physicians will document their gain in case management through the additional portable EEG and determine their disposition for their patient. In doing so, they will decide for themselves which of the possibly discordant EEG findings they consider superior. Since they know both findings and the patient, their two EEG assessments are not independent of each other.

The result of the second opinion in KNEU is subsequently included for the method comparison.

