#### Feasibility study phase

The question of whether one of the two diagnostic procedures indicates for more or fewer patient-targeted referrals or therapies will be tested using a McNemar test.^3^ In a proportion of discordances in the one direction of 0.1 and in the other direction of 0.05 (i.e., 15% of the patients are discordant), and based on the conventional statistical assumptions (error of the first type < 0.05, power > 0.8), a difference between the two procedures can be statistically confirmed with 468 double-diagnosed patients. In the case of 20% discordant patients (with proportions of 0.13 vs. 0.07), 433 patients would be sufficient. For the feasibility study phase, therefore, we expect there to be a duplicate diagnosis for 500 patients.

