**Fig. 1 Fig1:**
[figure not shown]
Process sequence of data management, blinded second assessment (KNEU) and conciliary feedback to private practitioner

In the review of the EEG findings from the practice and the KNEU, there will be two four-fold tables (Table 5).

**Table 5 Tab5:** EEG assessments by the University Department of Neurology (KNEU) in relation to the previous assessment by the private practitioners

	Practice assessment		
Assessment KNEU	Action (2B, 2C)	No action(2A)	Total
Conventional practice EEG			
Action (1B, 1C)	a	b	a + b
No action (1A)	c	d	c + d
Total	a + c	b + d	a + b + c + d
Portable EEG			
Action (1B, 1C)	a	b	a + b
No action (1A)	c	d	c + d
Total	a + c	b + d	a + b + c + d

The first result criterion will be the proportion and the direction of the cases with discordant disposition of the two EEGs by the private practitioner (Table 3). The second criterion will be the proportion and direction of discordant results in the treatment regimen by specialists of KNEU within the framework of the pseudonymized second assessment.

In this way, it will be possible to determine how the KNEU physicians assess the portable EEG differently from the private practitioners in addition to generating insights into how these two physician groups differ from each other in terms of their assessments of the office-based EEG. Furthermore, it will be possible to observe how the assessments of the consulting physicians from KNEU differ from each other. These assessments will each be quantified as kappa values.

As a third result criterion and final evaluation level of method comparison, the original four-fold table will be prepared again after the consolidation of the first and second assessments (Table 6):

**Table 6 Tab6:** Consolidated EEG assessments jointly by the University Department of Neurology and by the private practitioners

Practice-EEG^a^	Portable EEG^b^		Total
	Action (2B, 2C)	No action(2A)	
Action (1B, 1C)	a	b	a + b
No action (1A)	c	d	c + d
Total	a + c	b + d	a + b + c + d

^a^
http://powerandsamplesize.com/Calculators/Compare-Paired-Proportions/McNemar-Z-test-2-Sided-Equality

^b^After consolidation of the initial assessment in practice and the second assessment in the University Department of Neurology

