## Discussion

The advantage of the described procedure is that it can be immediately transferred and implemented in the outpatient routine care setting. The diagnostic yield will be examined by following a randomized approach. Therapeutic consequences will be legally and practically left to the discretion of the private practitioner. Therefore, no final consensus among the physicians involved in the EEG assessments will be required and, even less, can therapeutic consequences be randomized. To this extent, the medium-term benefits for the patient cannot yet be estimated with the presented design.

The technically extended EEG can lead to an increase in the indication and, thus, to an increase in diagnostic and therapeutic performance. On the other hand, unclear referrals and hospital and sleep-patient stays are likely to reduce. The case documentation will record the planned follow-up dispositions. This will allow a comparative calculation of the statutory health care costs of the two EEG modalities. A medium-term cost-benefit assessment at the level of the health insurance funds or society will not be possible with this design.

It is anticipated that the HOME^ONE^ study can help to increase patients’ acceptability of EEG home-monitoring. We expect the study will shed light on the question of whether such home-monitoring leads to sufficient change of management cases. The feasibility study phase, in particular, will facilitate the identification of particularly relevant medical indications or suspected diagnosis for the use of the EEG home-monitoring. Based on the results, the objective of the *HOME* project is to design and perform indication-specific full-scale randomized controlled trials.

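### The proportion of discordant dispositions is read as change of management with no reading-noise benchmark; two readings of one EEG could give a share of similar size

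*Protocol article*

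**What the plan says.** The result criteria are in the section on the randomized second assessment by KNEU, below Table 5. The first reads: "The first result criterion will be the proportion and the direction of the cases with discordant disposition of the two EEGs". Here one practising neurologist codes both recordings, and Table 3 holds the counts. For the second, the same quantity comes from the KNEU specialists' pseudonymized reading. The third rebuilds the fourfold table after practice and KNEU assessments are consolidated (Table 6).

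The article gives these tables a meaning:
- In Data analysis and measures, of Table 3: "This represents an intra-individual method comparison with a binary result criterion", which is named change of management.
- In the Background, such changes "reflect the therapeutic yield of a patient-controlled EEG home-monitoring".
- In the Discussion, the study is expected to show "whether such home-monitoring leads to sufficient change of management cases". The Abstract and the objectives make sufficient evidence of yield the justification for full-scale studies.

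On reader agreement, Study phases and settings states: "The inter-rater reliability of EEG evaluations shows kappa values of 0.5 to 0.9", depending on the question. The sample size section for the feasibility phase plans for 0.10 against 0.05 ("15% of the patients are discordant") and, as an alternative, 0.13 against 0.07 (20%).

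**The concern.** A two-category code that is not perfectly repeatable produces off-diagonal cases even when both recordings carry the same information. In Table 3 and its successors those cases fall into cell b or cell c, and a case in c looks like a patient whose management the portable EEG moved forward. The plan does quantify reader agreement, through kappas between practice and KNEU and between the two KNEU readers. It reports these separately and does not use them to interpret the between-device proportion. The McNemar test compares c with b, so it addresses net direction and leaves the size of b + c uncorrected.

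The risk is that a discordance of the size the plan expects is reported as yield, and cited in support of full-scale trials, when part or all of it is what re-reading one EEG would give.

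**Working it through.** **1. The plan's own figures.** McNemar sample size, with D = sum and d = difference of the two discordant proportions, two-sided 5%, power 80%: n = [1.960·√D + 0.842·√(D − d²)]² / d².
- 0.10 against 0.05: D = 0.15, d = 0.05, n = 468.6 (article: 468).
- 0.13 against 0.07: D = 0.20, d = 0.06, n = 433.7 (article: 433).

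Both reproduce. These are sample-size assumptions, and no threshold for sufficient yield is attached to them.

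**2. Discordance from one EEG read twice.** Kappa is 1 minus observed disagreement over chance disagreement. If both readings have Action share p, chance disagreement is 2p(1−p), so discordance = 2p(1−p)(1−kappa). Kappa comes from Study phases and settings. The Action share is not given and is assumed to lie between 0.1 and 0.5.

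| p | kappa 0.5 | 0.6 | 0.7 | 0.8 | 0.9 |
|---|---|---|---|---|---|
| 0.1 | 9.0% | 7.2% | 5.4% | 3.6% | 1.8% |
| 0.2 | 16.0% | 12.8% | 9.6% | 6.4% | 3.2% |
| 0.3 | 21.0% | 16.8% | 12.6% | 8.4% | 4.2% |
| 0.4 | 24.0% | 19.2% | 14.4% | 9.6% | 4.8% |
| 0.5 | 25.0% | 20.0% | 15.0% | 10.0% | 5.0% |

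**3. Where noise alone equals the planned discordance.** Solve kappa = 1 − x / [2p(1−p)].
- x = 15%: kappa at or below 0.53 (p = 0.2), 0.64 (0.3), 0.69 (0.4), 0.70 (0.5).
- x = 20%: kappa at or below 0.52 (p = 0.3), 0.58 (0.4), 0.60 (0.5). At p = 0.2 it would need 0.375, outside the quoted range.
- At p = 0.1 neither figure is reached within the quoted range.

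**4. Effect on the test.** With symmetric noise of 5% to 25% and N = 500, the simulated McNemar rejection rate is about 5%, so noise does not create a net difference. Half of it lands in cell c: 7.5% of patients if the discordance is 15%. If noise came on top of the planned 0.10/0.05, power at N = 500 would fall from 82.5% to 71% (5 points more discordance) or 61% (10 points more). The planning figures may already include some noise.

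**5. What isolates the recordings.** For one patient let readers 1 and 2 code Action with probabilities u_C, u_P and v_C, v_P on the conventional (C) and portable (P) EEG, independently given the recordings. Each disagreement rate below is averaged over its two reader-device pairings.
- Different device, different reader: ½[u_C + v_P − 2u_C·v_P + u_P + v_C − 2u_P·v_C].
- Same device, different reader: ½[u_C + v_C − 2u_C·v_C + u_P + v_P − 2u_P·v_P].

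The difference is (u_C − u_P)(v_C − v_P). It is zero when the two recordings lead to the same coding, however noisy the readers are.

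**The case against.** The strongest reply is that the quoted kappas do not fit the first criterion. They are between raters and concern EEG evaluations, whereas Table 3 holds Action/No action codes set by one practitioner for both EEGs. The article itself says: "Since they know both findings and the patient, their two EEG assessments are not independent of each other". This stands: the table above cannot be taken as the noise in Table 3. Carry-over between the two codes may lower it or distort it, and the article gives nothing to measure it by. Table 6 follows consolidation between practice and KNEU, so it is not a pair of single readings either. For the second criterion, KNEU differences are settled jointly after re-identification, which may remove part of the noise; the single-reading figures are then on the high side.

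A second reply is that the plan does not equate yield with b + c. It separates c from b, names direction in the criterion, tests it with McNemar, and has practitioners document their gain separately. This also stands for direction. But proportion is named alongside direction, and the article declines at this level to rank c above b, so the size of the discordance remains a result in its own right.

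A third reply is that the pilot calibrates readers and that kappas are planned in both phases. These describe the readers; they set no reference rate for the between-device proportion.

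**Conclusion.** The point holds in a limited form. The proportion of discordant dispositions cannot be interpreted as yield without a reading-noise benchmark, and the article provides none. For independent readings, noise could account for about 2-25% discordance. It matches the planned 15% only with kappa at or below about 0.5 to 0.7 and an Action share of about 0.2 or more, and the planned 20% only with kappa up to about 0.6 and a share of about 0.3 or more. At kappa 0.8 it is at most 10%, at 0.9 at most 5%. These figures assume equal Action shares in both readings, that the quoted kappas apply to dispositions, and an Action share the article does not state.

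A reader might infer that reading noise would by itself produce the expected discordance, or that it invalidates all three criteria and the McNemar test. The documents do not support that. The upper part of the quoted kappa range gives clearly less than 15%. The kappas bear most directly on the KNEU criterion and leave the noise in Tables 3 and 6 unknown. Symmetric noise cancels in the comparison of b with c.

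**What to change.** 1. Have each KNEU reader record an Action/No action code for each EEG before re-identification and joint resolution. The article says both experts judge both EEGs independently on the standardized form, but does not state that a disposition code is fixed at that stage.
2. For the second criterion, report different-device/different-reader discordance minus same-device/different-reader discordance, paired by patient, with its confidence interval. Show same-reader/different-device discordance alongside.
3. Base any statement that change of management is sufficient on this excess together with the direction (c against b), not on raw b + c. Direction is needed because the excess also counts patients in whom the portable EEG falls behind.
4. State that Tables 3 and 6 have no direct noise benchmark and that their raw proportions are descriptive. The KNEU excess informs them only indirectly.

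The cost is one recording step, one more analysis and a table. No further patients or readers are needed. The reported yield will be smaller than the raw discordance.

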### Data analysis and measures

Comparing the two EEG recording methods, the conventional practice EEG cannot be the gold standard to determine the sensitivity, specificity, and predictive values of the portable EEG. The goal that underpins the use of the portable EEG is to gain additional diagnostic insights through extended use. However, in the present state of the method, the portable EEG can remain behind the conventional practice EEG in its diagnostic yield, for example, due to increased artifacts or errors in handling by the patient. As such, it will be necessary to document the technical assessment and the extent to which there is concordance between the two EEGs.

In the pilot study phase, all three assessors will evaluate the technical quality of the EEG records according to the following ratings:The EEG record is unrestrictedly for medical reporting,The use of the EEG record for medical reporting is limited, andThe EEG record is not usable for medical reporting.

The evaluation of the technical quality is based on different criteria:The assessor’s overall impression on the EEG record,The frequency of artifacts,Strength of 50 Hz line noise, andRecovery of EEG traces after strong artifacts.

These criteria meet the standards of the International Federation of Clinical Neurophysiology (IFCN) for digital recording of clinical EEG [15].

In addition, all three assessors will document their medical reports for each blinded EEG record. After re-identification of the EEGs and the associated medical reports by the Data Trustee, the concordance (or discordance) will be evaluated. As measurements, we will use concordance rates and kappa values.

In the feasibility study phase, we will use the same approach. However, we will extend it as follows: To share information regarding a possible change of management, the private practitioner will classify the results of the conventional practice EEG according to the possibilities presented in Table 1.

**Table 1 Tab1:** Action-oriented classification of the findings of the conventional practice EEGs

1A	No action or follow-up appointment only
1B	Targeted referral for further clarification or co-treatment or further treatment
1C	Initiate or change therapy (adjust, switch, settle)

In the same way, they will also classify the results of the portable EEG (see Table 2).

**Table 2 Tab2:** Action-oriented classification of the results of the portable EEG

2A	No action or follow-up appointment only

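### Practice–KNEU differences are summarised only as kappa, which has no direction and moves with the Action share; name a paired difference from the planned Table 5 beside it

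*Protocol article*

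**What the plan says.** All references are to the Protocol article.

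- **Question.** Randomized second assessment by KNEU, text after Table 5: "it will be possible to determine how the KNEU physicians assess the portable EEG differently from the private practitioners". The same sentence asks how the two groups differ on the office-based EEG, and the next one asks how the KNEU readers differ from each other.
- **Index.** The paragraph closes with "These assessments will each be quantified as kappa values". It names no other measure.
- **Display.** "In the review of the EEG findings from the practice and the KNEU, there will be two four-fold tables (Table 5"), one for the conventional and one for the portable EEG. Rows are KNEU, columns are practice, and all four cells and both margins are shown.
- **Direction within each reader group.** "The first result criterion will be the proportion and the direction of the cases with discordant disposition of the two EEGs by the private practitioner". "The second criterion will be the proportion and direction of discordant results in the treatment regimen by specialists of KNEU".
- **General agreement measures.** Data analysis and measures, pilot phase: "As measurements, we will use concordance rates and kappa values". For the second phase: "In the feasibility study phase, we will use the same approach", with extensions.
- **Status of the two readings.** The same section concedes that the practitioner knows both findings and the patient, so the practitioner's two assessments are not independent. Privacy and ethics says that pseudonymisation makes KNEU assess the two EEGs independently of each other.

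**The concern.** The question is directional: on which EEG does one group call Action more often than the other, and by how much? Kappa measures chance-corrected agreement. It treats a practice that calls Action more often than KNEU and one that calls it less often as the same result. The concordance rate carried over from the pilot phase has the same blind spot.

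Kappa also depends on the margins. The sizing scenarios assume that the Action shares of the two EEGs differ. The two panels of Table 5 could then give different kappas even with equally accurate readers, and a reader of the report could take that for a device or reader effect.

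This matters more here than in a routine agreement study. The practice reading is made with knowledge of device, patient and both findings, while the KNEU reading is pseudonymised. Comparing the two is the design's own means of checking whether that knowledge tilts the practice reading towards Action on the cap, and kappa cannot express such a tilt.

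**Working it through.** **Figures in the documents.** The kappa sentence carries no figure, and no Action share, reader accuracy or practice–KNEU discordance rate is given anywhere. The only related figures are those for the McNemar test (Sample size calculation, feasibility phase). With the two-sided formula n = [1.96·√(p10+p01) + 0.8416·√(p10+p01−(p10−p01)²)]²/(p10−p01)²:

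- 0.10 and 0.05 give 468.57 (stated 468).
- 0.13 and 0.07 give 433.68 (stated 433).

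Both agree apart from rounding. They imply a gap in Action share between the two EEGs of 0.10 − 0.05 = 5 points, or 0.13 − 0.07 = 6 points. Everything below is illustration on assumed inputs.

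**1. No direction.** For a Table 5 panel, b is KNEU Action with practice No action, and c is the reverse. With po = (a+d)/n and pe the agreement expected from the margins, kappa = (po − pe)/(1 − pe). Assume n = 500.

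| (a, b, c, d) | KNEU Action | Practice Action | po | pe | kappa | (b−c)/n, 95% CI |
|---|---|---|---|---|---|---|
| 100, 60, 10, 330 | 32% | 22% | 0.86 | 0.6008 | 0.649 | +0.10 (0.068 to 0.132) |
| 100, 10, 60, 330 | 22% | 32% | 0.86 | 0.6008 | 0.649 | −0.10 (−0.132 to −0.068) |

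Here pe = 0.32·0.22 + 0.68·0.78 = 0.6008 and kappa = 0.2592/0.3992. The interval is ±1.96·√[(b+c) − (b−c)²/n]/n = ±1.96·√65/500 = ±0.032. Kappa and the concordance rate are the same in both rows; only the paired difference separates them.

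With a = 150, d = 275 and 75 discordant patients, kappa stays between 0.680 (split 37/38) and 0.687 (split 75/0 or 0/75). It hardly registers how one-sided the disagreement is.

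**2. Dependence on the Action share.** Assume two conditionally independent readers with sensitivity = specificity = 0.90. Agreement is 0.9² + 0.1² = 0.82 at every true share π. The observed share is m = 0.1 + 0.8π, and pe = m² + (1−m)².

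| π | m | pe | kappa |
|---|---|---|---|
| 10% | 18% | 0.7048 | 0.390 |
| 15% | 22% | 0.6568 | 0.476 |
| 30% | 34% | 0.5512 | 0.599 |
| 50% | 50% | 0.5000 | 0.640 |

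The relevant comparison is a 5-point gap, not the whole range. Raising m by 5 points moves kappa as follows:

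- 0.390 to 0.492 (+0.10) from π = 10%
- 0.532 to 0.579 (+0.05) from π = 20%
- 0.599 to 0.622 (+0.02) from π = 30%
- 0.631 to 0.639 (+0.01) from π = 40%

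The size depends on the model. If b/c is held at 50/25 in 500 (85% agreement), kappa is 0.17, 0.41, 0.53, 0.64 and 0.70 at mean observed Action shares of 10, 15, 20, 30 and 50%. The slope at very low shares is then steeper.

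**3. What the planned data already contain.** Write K and P for the KNEU and practice Action shares, and p and c for portable and conventional. The portable panel of Table 5 gives K_p − P_p and the conventional panel gives K_c − P_c. Their difference is

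(K_p − P_p) − (K_c − P_c) = (K_p − K_c) − (P_p − P_c).

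The right-hand side is the net direction of criterion 2 minus that of criterion 1. The identity holds on the same patients and with the same KNEU reading in both places. A negative value means that the practice reading favours Action on the cap more than the KNEU reading does.

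**The case against.** The strongest reply is that kappa does not stand alone. Table 5 shows b, c and both margins for each EEG, and criteria 1 and 2 state direction within each reader group. By the identity above, both components of the tilt are already planned results. This stands. A reader might infer that the plan cannot show how the two groups read the cap differently, or that the tilt would go unmeasured. The documents do not support either reading: what is absent is a named paired difference, the explicit subtraction and an interval.

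Second, the protocol announces no test or comparison of the two kappas and attaches no threshold to them. That also stands. Non-comparability is therefore a caution on interpretation, not an error in a planned analysis.

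Third, the 10–50% range of Action shares far exceeds the 5–6 points used for sizing. For a 5-point gap in the first model, the shift is at most about 1.3 standard errors of a difference between two such kappas at n = 500, treated as independent (0.10 against about 0.08), and below one at higher shares. This limits the size of the problem but does not touch the lack of direction.

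Fourth, intervals and additional agreement measures are commonly left to an analysis plan, and kappa is a conventional inter-rater index that suits the comparison of the two KNEU readers. This is fair as far as it goes. But the article does choose an index for the practice–KNEU question, and that index cannot answer it.

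**Conclusion.** The point holds in a limited form. Kappa is the only index named for the practice–KNEU differences, and it cannot say which group calls Action more often; the concordance rate cannot either. This follows from the algebra and needs no assumption about the data.

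The dependence on the Action share is real, but its size is uncertain because the documents give neither Action shares nor reader accuracy. With assumed accuracy of 0.90, a 5-point gap shifts kappa by about 0.1 at low shares and by about 0.02 or less from about 30%. The portable and conventional kappas are therefore not strictly comparable if the Action shares differ, although the distortion may be small.

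No directional data are missing and no sample size depends on this. It is a worthwhile, inexpensive improvement to a descriptive analysis. It gains weight because the practitioner's two readings are admittedly not independent while KNEU's are pseudonymised.

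**What to change.** In the paragraph after Table 5, add the following:

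1. For each panel, report the Action share of KNEU and of the practice, and the paired difference (b − c)/n (KNEU minus practice) with a 95% CI, beside kappa. Positive and negative agreement are optional additions.
2. Report the portable-minus-conventional difference of these two paired differences with a patient-level CI, for example by bootstrapping patients. State that it equals the net direction of criterion 2 minus that of criterion 1 on the same patients, and that a negative value means the practice reading favours Action on the cap more than the blinded KNEU reading does.
3. State which KNEU reading enters Table 5 (the independent readings or the joint decision after re-identification), and use the same one in criterion 2, so that the identity holds and the contrast is correctly described.
4. Keep kappa as a secondary figure, and as the measure of agreement between the two KNEU readers. Do not interpret a difference in kappa between the panels as a device or reader effect.

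The cost is a few sentences of analysis wording. All quantities come from data already planned, with no new data collection and no change to either sample size.
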